### MyBack group

Patients in the MyBack group will participate in a patient-centred, tailored exercise programme informed by a behavioural change approach in addition to receiving usual care in their HU. The MyBack intervention programme will consist of 12 bi-weekly sessions (60 min each) over 6 weeks complemented by 12 exercise sessions to be carried out autonomously by the participants over the following 6 weeks (If the exercise programme includes an aerobic component, a third home-based exercise session will be included).

An initial clinical appointment will be scheduled to assess participants’ physical performance using specific tests, namely: aerobic capacity (6-minute walk test) [40], trunk (trunk flexor test, side bridge, Biering-Sörensen test) [41–44] and lower limb resistance (60s sit to stand test) [45], trunk and lower limb flexibility (sit-and-reach test, flexion and extension Schober test, Modified Thomas test) [46–48] and motor control (aberrant movement pattern and prone instability test) [49, 50]. Based on this assessment and on principles of exercise prescription (FITT-VP principles) [51], a tailored and structured exercise programme will be implemented. Therefore, the exercise component of the MyBack programme may include a variety of types of exercise including aerobic, strength, motor control or flexibility exercises. For example, if changes in motor control are not found, the participant will not perform motor control exercises, and emphasis will be placed on the other altered physical performance components.

All exercise sessions will be complemented with a behavioural change component aimed at promoting the adoption of the exercise programme (supervised and autonomous). This component aims to empower participants to integrate exercise and/or physical activity into their daily lives. Behavioural change component will be also tailored as physiotherapists will adjust content, delivery modes and behavioural change techniques to participant preferences and to individual determinants for target behaviour. Physiotherapists and participants will have access to documentation that will support the implementation of the MyBack exercise programme, including an online patient education package with key messages and BCTs (Physiotherapists) as well as videos supporting its exercise component (Physiotherapists and participants).

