### Data collection and outcomes

#### #Aim I: effectiveness

Two trained researchers, blind to the patients’ group, will be responsible for the organization and data collection process. Every 30 days after the date of randomization, and over a 1-year period, the participants of both groups will receive a text message (SMS API (twilio.com)) with a yes/no question regarding LBP recurrence (In the last month did you have pain in your back, with an intensity equal or greater than 2, on a scale where “0” means no pain and “10” the worst pain imaginable and lasting at least 24 h?). This question is based on the definition of LBP recurrences: “the return of LBP with a minimum duration of 24 hours, with a pain intensity ≥ 2 on an 11-point numerical scale, preceded by a minimum period of 30 days without pain” [53]. All text messages will be sent and received through a specific SMS platform. In the presence of a LBP recurrence, the researchers will contact the participant by telephone to answer to a brief survey concerning the date of the recurrence and its impact (if the episode was severe enough to limit activity and/ or to cause care seeking), and to fulfil the self-reporting instruments (Table 1).

In the absence of a LBP recurrence, the researchers will contact the participants at three fixed data points: 3, 6 and 12 months after baseline, to fulfil the NPRS, Roland-Morris Disability Questionnaire (RMDQ), Musculoskeletal Health Questionnaire (MSK-HQ) and EuroQol (EQ-5D-3 L) (Table 1). The estimated patient’s burden to answer all the questionnaires is approximately 15 min. In addition, the participants’ medical records will be reviewed every 3 months. Data on any additional medical consultations, medication or imaging tests prescribed, referral to other interventions or to other medical specialities or services or sickness certificates will be recorded on the patient’s CRF.

Participants will remain on the trial unless they choose to withdraw consent, or they fail to answer three consecutive follow-up text messages. To prevent withdrawals and when a participant does not answer to 3 SMS text message or is not available at fixed follow-up time points, a maximum of three additional attempts will be made by telephone call.

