#### #Aim II: implementation

A mixed methods approach will be implemented in parallel with the effectiveness study and will help to understand the study processes or underlying mechanisms in relation to context, setting, professionals and patients. The exploration of feasibility, acceptability, fidelity, and contextual determinants of change is expected to provide knowledge that will improve the success of the implementation of different study tasks, such as the delivery of a training programme for physiotherapists or the provision of care. This stage will be informed by the Behaviour Change Wheel guidance [37]. Additionally, this knowledge will provide an opportunity for future triangulation of data obtained from other study stages and data. For this purpose, information about the perceptions and experiences of all stakeholders, namely patients, health professionals and HUs coordinators, and participation data will be collected. This phase will be informed by the Medical Research Council (MRC) guidance for the development and evaluation of complex interventions and the conceptual model of implementation research proposed by Proctor et al. (2011) [61] as well as the RE-AIM Planning and Evaluation framework [62] to evaluate implementation outcomes and its potential to scale-out across primary care.

Focus groups with patients, health professionals and HUs coordinators, will be carried throughout the implementation of MyBack study. Focus groups with HUs coordinators and health professionals will be focused on the exploration of their perceptions regarding the feasibility, acceptability, and fidelity of delivery of the intervention, considering the competences needed as well as the resources available. Information about additional facilitators and barriers will be collected in order to identify contextual determinants of change that were not identified prior to implementation and should be addressed by the research team. Focus groups with patients will be held as they acknowledge them as active participants in health interventions. These focus groups will explore the fidelity of receipt, that is, fidelity with which the content of the intervention is received by patients, as well as the acceptability of the intervention, barriers, and facilitators for the maintenance of exercise in the long term.

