A total of 5 focus groups, including a minimum of 6 and maximum of 8 participants per group, will be carried out throughout the implementation of the MyBack study: 1 with HUs coordinators from the 3 PCC; 2 with health professionals from the 3 PCCs; 2 with patients. Thus, a minimum of 30 participants (6 HUs coordinators; 12 health professionals; 12 patients) are expected to be purposively selected from those who are going to participate in the study, by receiving or delivering MyBack programme or coordinating services for its implementation. To be included, patients are expected to have attended to a minimum of 12 treatment sessions. The focus groups will have an expected duration of 90 min per group and will be carried out by videoconference. All focus groups will be held by 2 researchers ([name]) with previous experience in facilitating focus group discussions. The discussions will be based on a semi-structured interview schedule previously developed and tested in pilot interviews. All focus groups will be audio-recorded and transcribed verbatim.

Additionally, study enrolment and participation data will be considered to evaluate the reach of the project in each practice by tracking the proportion of eligible patients referred to the study. Patients` adherence, defined as the completion of 12 or more treatment sessions, will be measured for all participants randomized into the MyBack group.

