#### #Aim I: effectiveness

To assess the effectiveness of the MyBack programme, a quantitative analysis of primary and secondary outcomes will be made using multivariable regression models. All quantitative analysis will be conducted by a statistician who will be masked to the intervention groups. The analyses will follow the intention-to-treat principle. Between-group differences for the primary outcome (risk of LBP recurrence) will be analysed using relative risk reduction (95%IC and significance level of *p* ≤ 0.05). Secondarily, survival curves for each group will be described and compared (log-rank test) using the days from randomization to the first episode of recurrence. Scores of pain intensity, disability, musculoskeletal health and HRQoL will be assessed for outliers, normality and homogeneity. In the case of parametric distribution, the differences between the two groups over time will be analysed using two-way repeated measures ANOVA. If significant, the Bonferroni post-hoc test will be used. In addition, a subgroup analysis will be performed according to potential differences between the participants who adhered or did not adhere to the experimental intervention.

The cost-effectiveness analysis will be developed from the perspective of the health care provider. All costs will be calculated for each participant and indexed in Euros for the reference year 2023. Quality-adjusted life years (QALYs) will be calculated with the EQ-5D, 5 L. Between-group differences for costs, QALYs and years of life gained will be analysed following the non-parametric bootstrap method. A cost-effectiveness analysis will be conducted using the incremental cost per QALY ratio.

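### The planned adherence subgroup rests on a cut-off reached after randomisation, so it is a non-randomised contrast that can lean towards benefit; the same cut-off under-represents early stoppers in the patient focus groups

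*Protocol article*

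**What the plan says.** All references are to the protocol article.

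- **Analysis** (Data handling and analysis plan, #Aim I: effectiveness). The general rule is "The analyses will follow the intention-to-treat principle". The plan then adds that "a subgroup analysis will be performed according to potential differences between the participants who adhered or did not adhere to the experimental intervention". It names no comparator or outcome for this, gives no method that recognises when adherence becomes known, and does not repeat a cut-off.
- **Definition** (Data collection and outcomes, #Aim II: implementation). Patient adherence is "defined as the completion of 12 or more treatment sessions, will be measured for all participants randomized into the MyBack group". No other definition of it appears.
- **Programme** (MyBack group). It consists of "12 bi-weekly sessions (60 min each) over 6 weeks complemented by 12 exercise sessions to be carried out autonomously" in the next 6 weeks, with a third home session if there is an aerobic component. That makes 24 or more sessions over 12 weeks.
- **Outcome clock** (Data collection and outcomes, #Aim I: effectiveness). Recurrence is asked about "Every 30 days after the date of randomization, and over a 1-year period". Follow-up therefore overlaps the whole programme.
- **Focus groups** (Data collection and outcomes, #Aim II: implementation). Part of the patient groups' task is to explore "the acceptability of the intervention, barriers, and facilitators for the maintenance of exercise in the long term". On selection: "To be included, patients are expected to have attended to a minimum of 12 treatment sessions".

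**The concern.** A subgroup in the usual sense is defined by something known at baseline, so randomisation holds within it. Adherence here is settled weeks after randomisation, in one arm only, while the primary outcome is already accruing. Someone whose back pain returns in week 3 may stop attending. The outcome then decides the group, and early recurrences move out of the adherers and into the non-adherers. Even without that route, people who keep attending may differ in prognosis from those who do not. A reader of the results could take the contrast as evidence that the programme works for those who do it, when it would look that way with no effect at all.

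The cut-off also has two readings. If treatment sessions means the supervised block, adherence requires all 12 of 12, and one absence makes a non-adherer. If any session counts, 12 of 24 or more is enough, and a participant who does no home exercise is adherent. The Background links the limited effects in two earlier trials to low adherence to mostly autonomous exercise, so the choice bears on the programme's own rationale.

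In Aim II, patients below the same threshold are the ones best placed to say why the programme was unacceptable or hard to keep up, and the sampling expectation works against hearing them.

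**Working it through.** The plan gives no figure for the adherence analysis. Its own sample size is sound and not at issue: for 40% against 20%, two-sided 0.05 and 80% power, the arcsine formula gives 81 per group as stated (pooled-variance formula: 82).

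**Inputs**

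- 12-month recurrence risk R = 0.40 (Sample size section).
- Programme effect: none, by construction, so any departure from RR 1 is bias.
- Assumed: constant hazard; b = 0.20 miss the cut-off for unrelated reasons; a share q of early recurrers who would otherwise have adhered stop and miss it.
- Window w in which a recurrence can still prevent adherence. At two supervised sessions a week, a full attender reaches 12 sessions by week 6 under either reading of the cut-off, so w = 6 weeks is the base case. Only slower attenders counting home sessions could still be affected up to week 12.

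**Formulas**

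- Early recurrence: e = 1 − (1 − R)^(w/52). For w = 6, e = 1 − 0.6^(6/52) = 0.0572; for w = 12, e = 0.1112.
- Adherent share: s = (1 − b)(1 − eq).
- Risk in adherers: (R − eq)/(1 − eq).
- Risk in non-adherers: [R − (1 − b)(R − eq)]/(1 − s).

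**Base case, w = 6, q = 0.5.** eq = 0.0286.

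- s = 0.8 × 0.9714 = 0.777.
- Adherers: 0.3714/0.9714 = 0.382.
- Non-adherers: (0.40 − 0.8 × 0.3714)/0.2229 = 0.1029/0.2229 = 0.462.
- RR = 0.382/0.462 = 0.83.
- Adherers against all controls: 0.382/0.40 = 0.96.

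| Window | Share stopping (q) | Risk, adherers | Risk, non-adherers | Spurious RR | Adherers vs all controls |
|---|---|---|---|---|---|
| 6 weeks | 0.25 | 39.1% | 43.2% | 0.90 | 0.98 |
| 6 weeks | 0.50 | 38.2% | 46.2% | 0.83 | 0.96 |
| 12 weeks | 0.25 | 38.3% | 46.0% | 0.83 | 0.96 |
| 12 weeks | 0.50 | 36.5% | 50.9% | 0.72 | 0.91 |

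**Sensitivity**

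- Crossing R = 40–60%, w = 6 or 12 and q = 0.25–1.0, with b held at 0.20, gives RR from 0.56 (40%, 12 weeks, 1.0) to 0.93 (60%, 6 weeks, 0.25). Every cell lies below 1.
- Unrelated non-adherence matters too. In the 6-week case at R = 40%, b = 0.10 gives 0.84 (q = 0.25) and 0.73 (q = 0.5); b = 0.30 gives 0.93 and 0.87.

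**Aim II, side by side.** The patient groups are to judge acceptability and barriers; the selection sentence expects at least 12 sessions attended. Patients who stopped before that are the group whose view of acceptability is likely to differ most, and they are the ones selected against. No arithmetic applies.

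**The case against.** The strongest reply is that nothing central is touched. Intention to treat governs the analyses, and the adherence sentence is an addition that speaks only of potential differences, so a descriptive comparison is a fair reading. The link to the 12-session definition is inferred, and an analysis plan that is not shown could supply the method. Much of this stands. The intention-to-treat results are unaffected, and the link is an inference, although to the only definition given. What does not fall away is that the article already fixes a subgroup analysis split by adherence and places it under effectiveness without calling it descriptive.

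A reader might infer several stronger things that the document does not support:

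- **That the trial's effectiveness result is biased.** It is not; only the additional contrast is.
- **That the bias is typically 0.72 or worse.** That needs recurrences in weeks 7–12 to push people below a threshold which full attenders have already passed.
- **That recurrence does cause stopping.** This is a plausible mechanism, not a statement in the protocol.
- **That early stoppers are never asked and barriers are missed altogether.** The focus-group rule is an expectation, not an exclusion. Barriers are also sought from professionals, coordinators and the earlier patient focus groups that inform development, though those earlier patients have not received the programme. Part of the patient groups' task, fidelity of receipt and long-term maintenance, does call for people exposed to it.
- **That the threshold means finishing the programme.** Twelve sessions may be only half of what is planned.

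**Conclusion.** The point holds in limited form. The adherence subgroup is a contrast on a variable that arises after randomisation, exists in one arm only and can be affected by the outcome. It cannot support an effectiveness claim. If recurrence leads some participants to stop, the error runs towards benefit: with no true effect, about 0.83 to 0.90 in the 6-week case, and 0.56 to 0.93 over the wider set of assumptions. Comparing adherers with all controls is biased less, 0.96 to 0.98 in the 6-week case, but in the same direction. Apart from the 40% risk, these sizes rest on assumed inputs: they illustrate, they do not predict. The intention-to-treat primary and secondary results stand. In Aim II the sampling expectation under-represents early stoppers, which weakens conclusions on acceptability and barriers without emptying them. This should be corrected, but it does not threaten the trial's main answer.

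**What to change.** 1. State that intention to treat is the only effectiveness result.
2. Replace the adherence subgroup with a complier average causal effect using randomisation as the instrument, reported both for the threshold and for number of sessions. Alternatively, keep the adherer/non-adherer comparison as descriptive only, with no effectiveness claim.
3. State whether treatment sessions means the 12 supervised sessions or any of the 24 or more.
4. Relax the attendance expectation so that purposive sampling for the two existing patient focus groups includes participants below 12 sessions.

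The changes are to wording only, with no added participants, visits or focus groups. The downsides should be written down:

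- The complier effect has a wider interval than the intention-to-treat effect.
- Its threshold version assumes that fewer than 12 sessions have no effect. If partial attendance helps, the estimate is inflated. The version by number of sessions replaces this with an assumption about the shape of the dose-response.
- It assumes no contamination of usual care. The protocol does not secure this: randomisation is of individuals within each health unit, all the physiotherapists are trained in the programme, and usual-care participants have an appointment with their physiotherapist.
- Patients who attended few sessions will be harder to recruit to focus groups.

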#### #Aim II: implementation

Qualitative data analysis will be performed in a similar way for all focus groups. The focus group discussions will be transcribed verbatim and anonymized by a researcher and then checked by a second researcher. An inductive thematic analysis will be used to achieve an in-depth data description through the identification, analysis and presentation of the relevant themes and subtheme. This analysis will follow the six phases described by Braun and Clarke (2006) [39]. In parallel, a deductive content analysis will be performed using a coding matrix based on the TDF domains and the COM-B components. The deductive analysis will be guided by the study’s aims of identifying barriers and facilitators to implementation of MyBack programme. Both analyses will be carried out independently by two researchers. A third researcher was approached to settle disagreements.

### Ethical issues and study supervisory group

Ethical approval was granted by the Ethics Committee of Regional Health Administration of Alentejo Central. The study will be conducted in compliance with the Declaration of Helsinki (1964 and amendments).

All potential participants will receive a participant information sheet with detailed information about “MyBack” study as well as contacts from research team for additional information, doubts or claims throughout the study. Those who agree to participate will be asked to give their written informed consent. All participants will be invited to participate voluntarily, and no economic retribution will be provided. No risks or discomforts are expected, since procedures for data collection will be based in self-reported measures, information from clinical records, text messages answers (yes/ no) or audio-records, and treatment will follow usual practice and current scientific recommendations. Nevertheless, safety reporting procedures will be in place to ensure any expected and unexpected serious adverse events, which could be deemed to be related to the study. Participants will be also informed about the possibility to withdraw at any moment. In this case, data associated with the participant will be erased.

All collected data will be securely stored with restrict access from the research team. Data will be kept in a locked file in a research building. All data will be preserved for a maximum of 5 years after the end of the study and then will be destroyed. Personal data will be managed following the privacy policy of leader institution and the General Data Protection Regulation (GDPR) established by the European Union diploma 2016/679.

A committee (Study Supervisory Group) formed by 2 patients, 4 health professionals and 2 researchers will be formed to continually assess the quality standards of the study and scientific and technical deliverables from an end user and informed stakeholder perspective. They will provide suggestions for improvement and will actively participate in the analysis, write-up, and subsequent dissemination of the study findings.

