The primary outcome of the study will be the risk of LBP recurrence, i.e. the percentage of participants experiencing one or more episodes of LBP recurrence within a 12-month follow-up period. Secondary outcomes include pain intensity, functional disability, musculoskeletal health and HRQoL. Pain intensity will be measured by a NPRS (11-point version). The NPRS has proven to be valid and reliable in patients with LBP [54, 55]. Disability status and HRQoL will be evaluated through the Portuguese versions of the Roland Morris Disability Questionnaire (RMDQ) and the EQ-5D, 5 L. Both self-reported measurement instruments have been cross-culturally validated to Portuguese language and showed good to excellent psychometric properties [56, 57]. The Portuguese version of the Arthritis Research UK Musculoskeletal Health Questionnaire (MSK-HQ) will be used to measured musculoskeletal health and 12 related subdomains (pain severity, physical function, work interference, social interference, sleep, fatigue, emotional health, physical activity, independence, understanding, confidence to self-manage and overall impact). The original and Portuguese version of MSK-HQ showed adequate psychometric properties in people with musculoskeletal pain [58–60].

Costs data will be collected to both groups from medical health records, and they will consist of all back pain-related recourse used within primary health care by each participant. For the MyBack group, the costs related to the MyBack programme (costs per session; costs of training physiotherapists; costs of materials and transport) will also be collected.

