### Data handling and analysis plan

A data management plan will be developed in advance entailing data collection procedures, missing data management, coding, and entry of variables in the electronic database. An independent researcher blind to the intervention groups will be responsible for transferring the patients’ data to the electronic database. All data will be stored in a coded format and, thus, unreadable without the codebook previously developed and kept securely under principal researcher responsibility. A data audit will be conducted every 3 months. Discrepancies between original data and database, and missing data, will be checked and corrected. Any missing values will be accounted for using multiple imputation methods.

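### Erasing all data of participants who withdraw contradicts the intention-to-treat analysis and can delete primary-outcome events already recorded

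*Protocol article*

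**What the plan says.** Under Ethical issues and study supervisory group: "Participants will be also informed about the possibility to withdraw at any moment". The next sentence reads: "In this case, data associated with the participant will be erased". Erasure is therefore the automatic result of withdrawal and does not depend on a request. Nothing limits it to data not yet collected.

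The analysis text (Data handling and analysis plan, #Aim I: effectiveness) states: "The analyses will follow the intention-to-treat principle". The general part of that section adds: "Any missing values will be accounted for using multiple imputation methods".

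The primary outcome (Data collection and outcomes, #Aim I: effectiveness) is "the percentage of participants experiencing one or more episodes of LBP recurrence within a 12-month follow-up period".

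The same section has a separate rule on staying in the trial: "Participants will remain on the trial unless they choose to withdraw consent, or they fail to answer three consecutive follow-up text messages". For unanswered texts and missed fixed follow-up points, "a maximum of three additional attempts will be made by telephone call". It also says that "the participants’ medical records will be reviewed every 3 months".

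**The concern.** The primary outcome is binary and is settled at the first recurrence. Someone who recurs in month 2 and withdraws in month 5 has a complete primary outcome, and the erasure sentence removes it. The secondary log-rank comparison loses the same event. A participant without an event, who could have been censored at withdrawal, disappears from the risk set as well.

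An analysis of the records that remain covers only people who did not withdraw. If withdrawal is related to recurrence, and differently so in the two arms, the comparison is biased. Different patterns are plausible because the burden differs: 12 supervised and 12 autonomous sessions in the MyBack group, against one appointment of 15 to 20 minutes in usual care. Methodological challenges itself says that a 12-week programme for people without symptoms may raise dropout.

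An analysis plan written later cannot undo this, because it cannot recover erased records. The correction belongs in the protocol and the information sheet.

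**Working it through.** **Inputs from the article.** Sample size (Aim I: effectiveness): risks of 40% and 20% (relative risk 0.50), alpha 0.05, power 80%, 81 per group, 5% dropout during the programme plus 10% loss during follow-up, 93 per group recruited. Randomization and blinding: 1:1 allocation.

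**The plan's own figure.** A two-sided comparison of 40% with 20% needs 82 per group with pooled variance and 81 (80.3 rounded up) with the arcsine formula. Power at 81 is 0.799. The inflation is 81 × 1.15 = 93.15, the stated 93. The sample size reproduces and is not the issue.

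**Power.** Analysing all 93 per arm gives 0.851. Losing 15% leaves 93 × 0.85 ≈ 79 per arm and 0.789. That loss is modest, so bias is the main question.

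**Bias formula.** With n randomised, true risk p, w erased and r of those already recurred, the observed risk is (n·p − r)/(n − w).

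**Assumptions.** The article gives neither w nor r. I take w = 5 (93 × 0.05 ≈ 5, as if only the programme dropouts withdrew consent) and w = 14 (93 × 0.15 ≈ 14, as if all attrition were erased, an upper bound). The values of r are assumed throughout.

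**No true effect (40% in both arms), usual-care erasures at that arm's own risk.** Expected recurrences per arm are 93 × 0.40 = 37.2. Usual care stays at 0.40. In MyBack:

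| Erased (w) | Of whom recurred (r) | Observed MyBack risk | RR (true 1.00) | Approx. rejection rate (nominal 5%) |
|---|---|---|---|---|
| 5 | 5 × 10/14 = 3.57 | (37.2 − 3.57)/88 = 0.382 | 0.96 | 5.7% |
| 5 | 5 | (37.2 − 5)/88 = 0.366 | 0.91 | 7.5% |
| 14 | 10 | (37.2 − 10)/79 = 0.344 | 0.86 | 11% |
| 14 | 14 (extreme) | (37.2 − 14)/79 = 0.294 | 0.73 | 29% |

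The same number is erased in each arm. The rejection rate is Φ(z − 1.96) + Φ(−z − 1.96), where z is the observed risk difference divided by its pooled standard error. For example, in the second row z = 0.034/0.0733 = 0.465.

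**Planned effect (20% against 40%).** Expected recurrences are 93 × 0.20 = 18.6 and 37.2.

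- 14 erased per arm, each at its own arm's risk: (18.6 − 2.8)/79 = 0.20 and (37.2 − 5.6)/79 = 0.40, so RR = 0.50 and there is no bias.
- 14 erased in MyBack with 8 recurred, usual care at own risk: (18.6 − 8)/79 = 0.134, so RR = 0.134/0.40 = 0.34.
- 5 erased in MyBack at the same share (8/14, so 2.86): (18.6 − 2.86)/88 = 0.179, so RR = 0.45.
- 14 erased in usual care, all recurred, MyBack at own risk: (37.2 − 14)/79 = 0.294, so RR = 0.20/0.294 = 0.68.

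**Imputation.** Multiple imputation fills gaps in a record from what is known about that person. An erased participant has no baseline values, no earlier replies and no recorded recurrence, so nothing individual is left to impute from.

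**The case against.** **The number affected may be small.** The article does not say how much of the 15% is withdrawal of consent and how much is loss of contact. Stopping the programme is not the same as leaving the trial. Adherence is to be measured for everyone randomised to MyBack, and adherers are to be compared with non-adherers, so people who stop exercising are evidently meant to stay in the data. This stands. It limits the size of the problem but does not resolve the conflict for those who do withdraw.

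**The direction is not known.** A reader might infer that erasure must favour MyBack because its burden is greater. The documents do not support that. No section says that participants whose pain returns tend to withdraw, and Methodological challenges also notes that long follow-up may affect collaboration, which applies to both arms. The calculations above move either way, or not at all.

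**Text non-responders.** A reader might also infer that people who miss three texts have their data erased or are left out of the analysis. The article says neither. It ends their participation after telephone attempts, their earlier data may be kept, and imputation is planned. That is missing data and does not by itself breach intention to treat. One ambiguity remains: the calls are described as a way to prevent withdrawals, so it is unclear whether persistent non-response counts as a withdrawal and would trigger erasure.

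**Consent and data protection.** Erasure may be a deliberate commitment to participants. The section cites the GDPR, but for the management of personal data in general, and does not tie the erasure rule to it. A participant's right to ask for erasure can be kept without making erasure automatic.

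**Conclusion.** The contradiction between automatic erasure on withdrawal and the intention-to-treat analysis is explicit in the text, and imputation cannot repair it. Confidence in that conflict is high.

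The size of the resulting bias is conditional. If about 5 per arm were erased and the MyBack ones had mostly or all recurred, a true relative risk of 1.00 would appear as 0.96 to 0.91. The 0.86 for 14 erased with 10 recurred is an upper-bound illustration that treats all planned attrition as erased; the row with all 14 recurred is an extreme. Selective erasure in usual care dilutes the effect instead (0.68 in place of 0.50 if all 14 had recurred). Erasure unrelated to outcome leaves the relative risk unchanged.

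It should still be corrected before data are lost: erasure is irreversible, it can remove settled primary-outcome events, and the remedy is cheap. The rule on unanswered texts needs clarification only.

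**What to change.** Replace the erasure sentence in Ethical issues and study supervisory group with wording to this effect: withdrawal ends further contact and data collection; data collected up to that date are kept and analysed in the randomised group; data are erased only if the participant explicitly asks for it; the number of such erasures is reported by arm.

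In Data collection and outcomes, state that three unanswered texts do not count as withdrawal, that these participants stay in the analysis set with recorded recurrences counted, and that the 3-, 6- and 12-month calls are still attempted. The 3-monthly record review can supplement this. It shows care use and not the self-reported pain outcome, and the Background puts care seeking at 40% of people with a recurrence, so it would miss many.

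The cost is an ethics amendment, a revised information sheet and a few extra calls. Participants who consented under the erasure statement keep that right unless they re-consent.
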